### Biobank resource

Biomarkers discovery requires a critical mass of cross-sectional and longitudinal samples, along with high-quality associated data, all collected according to rigorous scientific criteria (Hulsen et al., 2019; Pepe et al., 2015). Research biobanks, highly organized repositories dedicated to the collection, processing, storage, and management of biological samples and their associated data in adherence to strict quality standards, have been established to address this critical need (Barnes and Watson, 2020; Annaratone et al., 2021). They ensure the ethical collection and use of these resources by adhering to legal frameworks (such as GDPR) and principles like FAIR (Findability, Accessibility, Interoperability, and Reusability). By providing well-characterized biological materials and comprehensive datasets, biobanks facilitate collaboration and represent a cornerstone for advancing scientific research (Malsagova et al., 2020).

UPO Biobank^1^ serves as the institutional research biobank of the University of Piemonte Orientale (UPO), housed at the Applied Research Centre Ipazia in Novara and integrated with the Regional Research Infrastructure Center of Autoimmune and Allergic Diseases (CAAD). UPO Biobank supports a wide range of research, including disease-specific investigations and population-based studies. It currently manages a repository of over 10,000 samples—including plasma, serum, urine, and PBMCs—collected from more than 3,000 participants.

Given its expertise in sample handling and its role in supporting molecular epidemiological research, UPO Biobank can significantly contribute to the IN-TeMPO study assisting participating centers in the systematic collection, processing, and storage of blood and other biological samples required by the study and facilitating the longitudinal assessment of blood biomarkers.

## Methods and analysis

### Sample collection and storage

As displayed in Figure 2, blood samples (12 mL) will be collected after overnight fasting in K_2_EDTA-containing tubes at the baseline and after the completion of active multidomain or self-guided interventions (12 months) from *n* = 1,662 subjects participating in the IN-TeMPO study, according to protocol 1. Protocol 1 will be applied in all clinical centers.

**Figure 2 fig2:**
[figure not shown]
Schematic representation of the protocols for sample collection, storage, and destination of use.

A 400 ul aliquot of whole blood will be frozen at−20°C for the assessment of ApoE genotype. The remaining blood will be immediately centrifuged (2000xg, 10 min, RT) to obtain plasma. Plasma will be aliquoted and frozen at−80°C until blind biomarker assessment or sample sending to laboratories responsible for carrying out the analyses.

For all collected samples, the analysis of p-tau217, NFL, GFAP plasma levels and of ApoE genotype will be performed in laboratories of the University of Milano-Bicocca and University of Florence, and that of IL-6 and GDF-15 in laboratories of the University of Bari and University of Piemonte Orientale.

In a subgroup of *n* = 100 subjects, recruited in the coordinating clinical center in Monza, protocol 2 will be adopted (Figure 2). According to protocol 2, blood samples (30 mL total, 24 mL in K_2_EDTA-containing tubes and 6 mL in lithium heparin tubes) will be collected after overnight fasting at the same time-points (baseline and after 12 months).

Besides the aliquots of whole blood and plasma described above, adjunctive whole blood (2 mL in headspace vials) and plasma aliquots will be prepared for the analysis of the additional plasma biomarkers (BDNF, ghrelin, IGF-1 and irisin), protein aggregation and volatilomic analyses.

For NMR-based metabolomics and FTIR-based molecular signature studies, plasma will be obtained as described above from whole blood with the anticoagulant lithium heparin, as requested by the specific methods (Beckonert et al., 2007).

Peripheral blood mononuclear cells (PBMCs) and erythrocytes will be prepared from 5 mL whole blood. More specifically, PBMCs will be isolated from whole blood by Lympholyte® (EuroClone) density gradient centrifugation. Briefly, blood samples will be diluted with the same amount of saline solution, layered on Lympholyte® and centrifuged (490 × g, 30 min, RT). PBMCs will be collected from the interface between plasma and Lympholyte®, washed with saline solution, and stored at−80°C in a cryoprotectant medium (RPMI 1640 + 10% fetal bovine serum) containing 10% dimethylsulfoxide (DMSO) until analysis of *γ*-H2AX. Erythrocyte pellets will also be collected, processed following glycerol-based cryopreservation (Rogers et al., 2018) and stored at−80°C for protein aggregate analysis.

Finally, 3 mL urine will be collected, aliquoted and stored at-20°C for volatilomic (2 mL in headspace vials) and protein aggregate analyses (1 mL).

The analysis of γ-H2AX and redox status, and the untargeted metabolic fingerprint and profiling will be performed in laboratories of the University of Milano-Bicocca. BDNF, irisin, IGF-1 and ghrelin plasma levels will be quantified in laboratories of the University of Bari. Untargeted volatilomics analyses in whole blood and urine and protein aggregates analyses in plasma/erythrocytses and urine will be done in laboratories of the CNR-IMM in Lecce.

### Biomarker analysis

ApoE genotype will be determined using DiaPlexQ™ Apolipoprotein E (ApoE) Genotyping Kit Real-Time PCR based assay (SolGent, Daejeon, Korea), after extraction of total DNA from whole blood with a commercial DNA extraction kit (Qiagen, Venlo, Netherlands).

Plasma p-tau217 levels will be measured with CLEIA (ChemiLuminescence Enzyme ImmunoAssay) using the Lumipulse® G600II instrument (Fujirebio), with a commercially available kit that includes specific quality controls.

NfL and GFAP levels will be measured with CLEIA (ChemiLuminescence Enzyme ImmunoAssay) using the Lumipulse® G600II instrument (Fujirebio) or the Simoa® (Single-molecule array) technology (Quanterix), instrument SR-X™, with commercially available kits that include specific quality controls.

IL-6, GDF-15, BDNF, ghrelin, IGF-1 and irisin plasma levels will be measured with commercially available ELISA kits (R&D Systems) via VICTOR Nivo™ multimode plate reader (Revvity, Waltham, MA, USA). Novel technologies, such as Simple Plex assay (Ella, ProteinSimple, Bio-Techne) for IL-6 and GDF-15, and high-throughput proteomics techniques (Olink platform) could also be used, according to manufactures instructions, for rapid and accurate processing of large number of samples or to gain more insight into identifying complex protein signatures, whenever needed.

Plasma NAD+/NADH, NADP+/NADPH and glutathione levels will be measured using microplate reader (Victor, ELx 800, Milano, Italy) with commercially available ELISA kits.

For γ-H2AX analysis, viable and untouched T cells will be purified from PBMCs by negative isolation (Dynabeads™ Untouched™ Human T Cells Kit, Thermo Fisher). Freshly isolated T cells will be cultured and expanded in a specific medium (CTS™ OpTmizer™ T Cell Expansion SFM, Thermo Fisher) in order to obtain frozen batches and for further analysis. Isolated T cells will be used to examine the phosphorylation status of histone H2AX, called γ-H2AX. Briefly, cells plated on 96-wells coated with fibronectin (FN), will be fixed with PFA and permeabilized with 0.1% (w/v) Triton X-100 solution diluted in PBS. γ-H2AX will be analyzed by using a H2A.X phospho S139 antibody-conjugated to Alexa Fluor® 488, followed by incubation with the nuclear stain 4,‘6-diamidino-2-phenylindole (DAPI). Fluorescence image analysis will be conducted on an Operetta CLS™ High-Content Analysis System (PerkinElmer, Waltham, MA, USA).

For the analysis of protein aggregates, aliquoted plasma and deglycerolized erythrocyte samples will be first investigated through thioflavin T (ThT) staining followed by immunofluorescence assay to confirm the presence of Aβ amyloid fibrils and/or aggregation. Twin samples of those revealing the ThT binding will be imaged by means of Nanosurf CoreAFM in air/tapping mode (after depositing ~50 μL or less of the sample on fresh cleaved mica substrate then allowing air drying). The size and morphology (ranging from spherical/annular oligomers, protofibrils/fibrils), the assembly patterns and prevalence of protein aggregates, from all conditions, will be quantified through analysis of height and phase-contrast AFM data.

On a parallel route, Cyclic Amplification of Aβ misfolding and aggregation will be performed exploiting the functional property of Aβ oligomers to seed the polymerization of monomeric Aβ. To this end, a commercial Aβ1-42 amyloidogenic peptide fragment will be used for *in vitro* aggregate production and aggregate free Aβ1-42 aliquots preparation. The experiment will be performed adapting to urine samples the protocol published by Salvadores et al. (2014), measuring ThT fluorescence at various time points reflecting the difference in the aggregation kinetic when it occurs.

For NMR metabolic analysis, frozen plasma samples will be slowly thawed at +4°C overnight and then mixed gently and centrifuged (3,400 × g, 3 min, +4°C) to remove possible precipitate. Aliquots of each sample will be transferred into 5-mm outer-diameter NMR tubes and mixed in 1:1 ratio with a phosphate buffer (75 mM Na_2_HPO4 in 80%/20% H_2_O/D_2_O, pH 7.4, including also 0.04% sodium azide). The NMR spectra will be acquired using a Bruker Avance III 600 MHz NMR spectrometer. The prepared plasma samples will be loaded onto a sample changer, maintaining the temperature of samples waiting to be measured at +20°C. Two NMR spectra will be recorded for each sample at 37°C. The first spectrum, an unedited presaturated proton spectrum, features resonances arising from all the sample components, including proteins and lipids within various lipoprotein particles. The second spectrum, a Carr-Purcell-Meiboom-Gill T_2_-relaxation-filtered spectrum, allows the suppression of the broad macromolecule and lipoprotein lipid signals, leading to enhanced detection of low-molecular-weight metabolites. Moreover, 2D total correlation spectroscopy (TOCSY) and heteronuclear single quantum coherence spectroscopy (HSQC) experiments will be acquired on a subset of samples to simplify resonance assignment (Beckonert et al., 2007; Julkunen et al., 2023). Metabolite identification and assignment will be performed with the support of 2D NMR experiments, the Human Metabolome Database, the Biological Magnetic Resonance Data Bank, and the SMA analysis tool^2^ integrated in MestreNova software.^3^ For metabolite quantification, the GSD (global spectrum deconvolution) algorithm, available in the MNova software package of Mestrelab will be exploited (Airoldi et al., 2016; Ciaramelli et al., 2017; Ciaramelli et al., 2018; Ciaramelli et al., 2023).

For the FTIR analyses, the frozen plasma sample will be thawed and centrifuged at 3400 × g, 3 min at +4°C. A few microliters of the sample will be deposited on the single-reflection diamond crystal of the system for measurements in attenuated total reflection (ATR, Quest, Specac). After the evaporation of the bulk water, absorption spectra will be collected by the Varian 670-IR spectrometer (Varian Australia Pty Ltd.) as previously described (Ami et al., 2019). The absorbance spectra and their second derivatives will be subjected to multivariate analysis as previously reported (Ami et al., 2021; Ami et al., 2019; Ami et al., 2024).

For volatilomic analysis, Volatile Organic Compounds (VOCs) from whole blood and urine samples collected in headspace vials will be extracted by headspace solid-phase microextraction (HS-SPME) according to an optimized protocol. Next, a Gas Chromatography/Mass Spectrometry (GC/MS) untargeted method for the analysis of VOCs profile of the biosamples, will be applied. The GC/MS analysis will be performed on a Shimadzu GCMS-QP2020X equipped with a split-splitless injector. A 624 gas chromatographic column (60 m x 1.40 μm x 0.25 mm) functionalized with a mid-polar stationary phase (6% Cyanopropyl-phenyl; 94% dimethyl polysiloxane) recommended for VOC analysis will be used. The identification of the volatile compounds is achieved by comparing mass spectra with those of the data system library (NIST 98, *p* > 80%). As a first approach, a semiquantitative method based on EPA 8260 Internal Standards Mix as internal standard will be used.

### Data analysis

Biomarkers value distribution and outliers will be checked. Logistic regression models will be used to predict AD using Lumipulse plasma p-tau217 > 0.14 pg./mL as a standard of truth, based on previously reported thresholds in Subjective Cognitive Decline ([name], [name], et al., Plasma and CSF biomarkers in Subjective Cognitive Decline: the BBRC Alzheimer at-risk (*Β*-AARC) cohort, personal communication at AD/PD™ 2025 Alzheimer’s & Parkinson’s Diseases Conference, April 1–5, Vienna). Biomarkers will first be tested individually as predictors (univariate models), and then in combination (multivariate models). Sensitivity, specificity, accuracy, and predictive values will be derived using Receiver Operating Characteristic (ROC) curve analysis. Optimal cut-offs will be determined based on the Youden index for univariate models. Differences in model performance (AUCs) will be assessed using the DeLong test. The influence of key demographic and genetic variables (age, sex, ApoE genotype) on biomarker distribution will be evaluated by including them as covariates in multivariate models. Adjusted and unadjusted models will be compared using Akaike (AIC) and Bayesian (BIC) Information Criteria.

Analyses of the main objective will include: (1) assess if baseline biomarkers levels can predict intervention response (e.g., heterogeneity of intervention effects) in order to identify biomarkers-based phenotypes/profiles with higher intervention benefits; (2) interventions effects on biomarkers levels; (3) relationship between change in biomarkers and change in clinical outcomes (cognition, frailty). Points 2 and 3 will help understand intervention effects on disease biomarkers and biological mechanisms of beneficial effects on different outcomes. Untargeted/exploratory-omics biomarkers will be analyzed with machine learning considering different predictors.

All *p*-values will be corrected for multiple comparisons using False Discovery Rate.

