### Study population

The recruiting phase is currently ongoing within the IN-TeMPO study (ClinicalTrials.gov ID NCT06248723, protocol article in preparation), a RCT harmonized with the WW-FINGERS network, involving 9 clinical Italian centers (2 in the North, 2 in the Center, and 5 in the South). Briefly, a total of 1,662 community-dwelling older adults at increased risk of dementia and with mild to moderate frailty will be enrolled, according to the following inclusion criteria: age ≥ 60 years, Primary Care Frailty Index score between 0.07 and 0.21, Cardiovascular Risk Factors, Aging, and Dementia Risk Score (CAIDE) ≥ 6, Clinical Dementia Rating scale (CDR) ≤ 0.5, presence of an increased risk of developing dementia due to family history and/or at least one modifiable risk factor. The recruited subjects will be randomized into two groups. The first group will receive multicomponent interventions focusing on nutrition, physical exercise, cognitive training, management of metabolic and vascular risk factors, social activities, oral health, and recommendations for quality sleep. The second group will engage in self-guided interventions and will receive suggestions through app-web or video tutorials on the same domains. Wearable devices will be assigned to enrolled subjects to obtain clinical parameters. Informatic resources and artificial intelligence tools will be adopted to collect, analyze and share data. The primary objective is to evaluate the 12-month effect of multidimensional interventions on cognitive performance through a battery of neuropsychological tests (mNTB) in the active vs. the self-guided intervention group. Secondary and explorative objectives include assessing the impact of multidimensional interventions on functional and physical performance, as well as on a panel of blood biomarkers of cognitive and functional decline.

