#### Sarcopenia and muscle exercise

Growth/differentiation factor 15 (GDF-15) is a member of the TGF-*β* superfamily that is highly expressed in muscle tissue and will be used as a biomarker of senescence. Its expression is low in healthy, young subjects, with a range of 200–1,200 pg./mL (Breit et al., 2011). However, there is a notable increase in cases of chronic or acute disease conditions that may be age-related (Conte et al., 2019; Conte et al., 2020b). Furthermore, it is associated with a range of other conditions, including muscle atrophy, neurodegeneration, mitochondrial disease, and aging itself, which is independent of an individual’s health status (Lee et al., 2022; Liu et al., 2021). Moreover, GDF-15 has been proposed as a biomarker for sarcopenia, a clinical condition characterized by muscle atrophy and weakness (Kim et al., 2020; Herpich et al., 2021). Indeed, several studies have demonstrated a positive correlation between elevated serum levels of GDF-15 and a decline in skeletal muscle quality (Semba et al., 2020). While mounting evidence suggests a link between GDF-15 and sarcopenia, the precise function of GDF-15 in the reduction of muscle mass and function remains uncertain.

As additional biomarkers of sarcopenia and senescence, in a convenience sample of 100 enrolled subjects we will assess brain-derived neurotrophic factor (BDNF), a neurotrophin that plays a role in maintaining brain function. The concentration of BDNF varies throughout the lifespan, with generally higher levels observed during childhood than during adulthood. However, BDNF levels tend to be higher in early adulthood, with a gradual decrease observed over time (Webster et al., 2006). BDNF has also been associated with the processes of muscle repair, regeneration, and differentiation (Kalinkovich and Livshits, 2015). Importantly, BDNF plasma levels significantly increase with physical exercise, further supporting the role of exercise therapy in the prevention of cognitive decline (Coelho et al., 2014; Tsai et al., 2018). Therefore, BDNF may serve as a potential surrogate marker of sarcopenia and muscle exercise.

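### The DeLong test has the wrong null distribution for single-biomarker versus combined models if both are fitted and evaluated on the same subjects

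*Protocol article*

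**What the plan says.** All of this is in the Data analysis section of the protocol article, unless noted.

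- Outcome: "Logistic regression models will be used to predict AD using Lumipulse plasma p-tau217 > 0.14 pg./mL as a standard of truth".
- Model sequence: "Biomarkers will first be tested individually as predictors (univariate models), and then in combination (multivariate models").
- Test of discrimination: "Differences in model performance (AUCs) will be assessed using the DeLong test". No pairs are listed and none are excluded.
- Covariate adjustment (age, sex, ApoE genotype) has its own tool: "Adjusted and unadjusted models will be compared using Akaike (AIC) and Bayesian (BIC) Information Criteria".
- Multiplicity: p-values "will be corrected for multiple comparisons using False Discovery Rate". No level is stated.
- Sample sizes: Study population gives "a total of 1,662 community-dwelling older adults". Sarcopenia and muscle exercise says that "in a convenience sample of 100 enrolled subjects we will assess brain-derived neurotrophic factor (BDNF"), and Table 1 lists further markers for a subgroup of 100.

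The article names no likelihood-ratio test, bootstrap, cross-validation or validation set for the logistic models.

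**The concern.** A combined model that contains a given marker is nested over that marker's own model. Going from single to combined models invites exactly this comparison, and DeLong is the only test named for an AUC difference.

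DeLong compares two AUCs as if they came from two distinct scores with a non-degenerate joint normal limit. If the added marker contributes nothing, the two fitted scores converge to the same ranking of subjects. The AUC difference and its estimated standard error then shrink at the same rate, and their ratio is not standard normal.

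At stake is the conclusion on whether a panel discriminates better than one marker. A test that rejects far too rarely can report no detectable gain where one exists. False discovery rate control cannot repair this, because it takes as input p-values that are already too large.

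**Working it through.** **Plan's own figure.** There is none to reproduce. The article gives no power, alpha, AUC or prevalence for this analysis, so the check is by simulation.

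**Inputs from the article.** N=1,662 for the all-subject markers (NfL, GFAP, IL-6, GDF-15); N=100 for the subgroup markers; binary outcome; logistic models; DeLong.

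**Assumptions, not in the article.** Prevalence of p-tau217 positivity 10, 20 or 30% at N=1,662, which is 1,662 × 0.10, 0.20, 0.30 = about 166, 332, 499 positives. At N=100 it is 20 or 30%, which is 20 or 30 positives. Base-marker AUC is 0.65-0.80 (0.70 and 0.80 only for d=0.4 and 0.5 and for three added markers). Markers are normal and independent within outcome groups. The added marker is shifted by d standard deviations in positives. Two-sided 0.05 per test, before false discovery rate control. Models are fitted and evaluated on the same data, with 500 to 2,000 replicates per setting.

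**Tests.**
- DeLong: z = (A2 − A1) / √(V1 + V2 − 2·C12), where A is the AUC of each fitted score, V its variance and C12 the covariance; reject if |z| > 1.96.
- Likelihood ratio: 2(ℓ2 − ℓ1), referred to χ² with degrees of freedom equal to the number of added markers.

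**Why z fails.** When the true added coefficient is 0, its estimate is of order 1/√n. The AUC is flat at its maximum there, so A2 − A1 is of order 1/n. The DeLong standard error of the difference is also of order 1/n, because the two sets of subject-level components differ only by order 1/√n. The ratio therefore has no standard normal limit.

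**Step 1: rejection when the added markers are useless (nominal 5%).**

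| Setting | DeLong | Likelihood ratio |
|---|---|---|
| N=1,662, one added | 0.0-0.3% | 3.6-5.8% |
| N=1,662, three added | 0.7-1.3% | 4.5-5.8% |
| N=100, one added | 0.2-0.5% | 5.0-7.4% |

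Control: two single markers with equal true AUC (non-nested, N=1,662, 2,000 replicates) give DeLong 5.1%. With 2,000 replicates the Monte Carlo standard error at 5% is √(0.05 × 0.95 / 2,000) = 0.5%, so the control is on target and the nested results are not. The fault is specific to nested pairs.

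**Step 2: power with one informative added marker.** Gains are mean in-sample AUC differences, so they include some optimism. With a useless marker the mean in-sample gain was 0.0003-0.0016 at N=1,662 and 0.005-0.017 at N=100.

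| N | d | AUC gain | DeLong | Likelihood ratio |
|---|---|---|---|---|
| 1,662 | 0.1 | 0.001-0.004 | 1-3% | 20-46% |
| 1,662 | 0.15 | 0.002-0.007 | 3-12% | 40-75% |
| 1,662 | 0.2 | 0.004-0.011 | 4-34% | 60-95% |
| 1,662 | 0.3 | 0.008-0.022 | 26-86% | 92-100% |
| 1,662 | 0.4 | 0.013-0.025 | 56-99% | about 100% |
| 1,662 | 0.5 | 0.019-0.038 | 81-100% | about 100% |
| 100 | 0.5 | 0.024-0.062 | 3-10% | 41-59% |
| 100 | 0.8 | 0.048-0.111 | 16-47% | 78-93% |

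The gain at which DeLong begins to detect depends on prevalence and base AUC. With base AUC 0.80 and a gain of about 0.008 (d=0.3), its power is 26, 51 and 72% at prevalences of 10, 20 and 30%. About 0.01 is therefore a rough guide, not a sharp limit.

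**Step 3: a second set-up.** Logistic data, N=1,662, prevalence 20%, base log-odds 0.8 per SD, 1,500 replicates. With an added log-odds of 0, DeLong rejects 0.1% and the likelihood-ratio test 5.4%. At 0.2 (gain about 0.007) power is 19% against 86%; at 0.3 (gain about 0.014) it is 64% against 99.7%. Extending this set-up to 0.4 and 0.5 (gains about 0.024 and 0.036, 600 replicates) gives DeLong 95% and 99.7%. Both set-ups agree.

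**The case against.** Five points can fairly be made for the plan.

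1. **The nested use is inferred.** The article lists no pairs, and DeLong is sound for NfL against GFAP alone. This stands as a limit: single against combined is the natural reading, not explicit text.
2. **Same-data evaluation is inferred too.** The full protocol or analysis plan may specify cross-validated or held-out AUCs, in which case the figures above would not apply. The point is therefore conditional on same-data evaluation.
3. **Adjusted against unadjusted models are not affected.** A reader might add these nested pairs to the problem. The article assigns them to AIC and BIC, which are likelihood-based and suit nested models.
4. **Coefficient tests may come anyway.** Testing markers in a multivariable logistic model normally yields them, and for one added marker they are asymptotically equivalent to the likelihood-ratio test. That is plausible, but the article names only DeLong for differences in model performance, so two answers could coexist with no rule for which decides added value.
5. **The consequence is limited.** The error is conservative, the AUC estimates themselves are untouched, and a non-significant result is not a finding of no gain. The gain of a panel over a single marker is not among the three main-objective analyses listed in Data analysis; Limitations mentions the possible accuracy of combinations only in explaining a budget-driven choice. This stands, and bounds the importance of the point.

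None of this makes the normal reference distribution right for a nested pair.

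**Conclusion.** The concern holds within limits. For a marker against a combination containing it, fitted and evaluated on the same subjects, the named test rejects about 0-1% of the time under the null instead of 5%. At N=1,662 this costs most of the power for AUC gains of about 0.01 or less, while most gains of about 0.025 or more are still found. At N=100, DeLong power stayed below 50% in every setting tried.

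A reader might infer that DeLong would miss most real added value in general, or that the trial would be bound to conclude that panels add nothing. The figures do not support that: at N=1,662 power is 56-99% at d=0.4 and 81-100% at d=0.5. Nor does the article make DeLong the sole criterion of added value.

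The null result rests on nesting and same-data evaluation. The power figures rest also on the assumed prevalence, base AUC, effect sizes, marker independence and alpha of 0.05. The primary comparison of cognitive performance (mNTB) is unaffected.

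**What to change.** State in the Data analysis section, or in the analysis plan, that:

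- the added value of biomarkers in nested models is tested with the likelihood-ratio test of the added coefficients;
- the AUC difference is reported as an optimism-corrected estimate (bootstrap or cross-validation) with an interval;
- DeLong is used only for non-nested comparisons, such as NfL alone against GFAP alone.

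The false discovery rate correction then applies to the likelihood-ratio p-values for these comparisons. AIC and BIC for covariate adjustment can stay. The cost is a sentence or two and a little computing, with no new data or participants. The article reports recruitment as ongoing, so the change can be made before analysis.

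### The influence of age, sex and ApoE genotype on biomarker levels is to be judged in models where the biomarker is a predictor, which do not estimate that influence

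*Protocol article*

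**What the plan says.** All the relevant text is in the first paragraph of the Data analysis section of the protocol article.

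- The dependent variable is set first: "Logistic regression models will be used to predict AD using Lumipulse plasma p-tau217 > 0.14 pg./mL as a standard of truth".
- The biomarkers are then put on the right-hand side, and the two model types are named: "Biomarkers will first be tested individually as predictors (univariate models), and then in combination (multivariate models".
- After the sentences on ROC curves, cut-offs and AUC comparison comes the aim at issue, that the influence of age, sex and ApoE genotype "on biomarker distribution will be evaluated by including them as covariates in multivariate models".
- The criterion follows at once: "Adjusted and unadjusted models will be compared using Akaike (AIC) and Bayesian (BIC) Information Criteria".

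The only other text on distributions is the paragraph's opening sentence, "Biomarkers value distribution and outliers will be checked". The three main-objective analyses in the next paragraph concern prediction of intervention response, intervention effects on biomarkers, and the relation of biomarker change to clinical change. No model with a biomarker level as the dependent variable and age, sex or ApoE genotype as explanatory variables is described.

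**The concern.** The aim is about what shifts a biomarker, so the biomarker is the quantity to be explained. In the models the paragraph describes, it is an explanatory variable and p-tau217 status is the quantity explained. Adding age to such a model asks whether age carries information about p-tau217 status beyond what the biomarker carries. That question is legitimate, but it is a different one.

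The two answers need not agree. A marker that rises steeply with age can leave age with nothing to add once the marker is in the model. A covariate unrelated to the marker can still improve the model because it predicts p-tau217 status by another route.

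The article's own background makes both situations plausible. It describes IL-6 as rising in older people (Neuroinflammation) and GDF-15 as associated with aging itself (Sarcopenia and muscle exercise), so real age dependence is expected. It describes ApoE ε4 as a major genetic risk factor for Alzheimer's disease (Genetic risk factor), so ApoE may well predict p-tau217 status without acting on NfL, IL-6 or GDF-15. At stake is whether the report on what drives these marker levels can be relied on.

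**Working it through.** The plan gives no figure for this step, so there is none to reproduce. The check is one of logic, illustrated by simulation.

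**Inputs from the document.** n = 1,662 (Study population: "a total of 1,662 community-dwelling older adults at increased risk of dementia and with mild to moderate frailty will be enrolled"); binary outcome p-tau217 status; biomarkers as predictors; adjusted and unadjusted models compared by AIC and BIC.

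**Assumptions, because the document gives no values.** Age is standard normal. Biomarker = r·age + √(1 − r²)·noise, so the true slope of biomarker on age is r. Logit P(status positive) = −1.6 + b·biomarker + g·age, which gives about 19 to 22% positive. Ranges: r from 0 to 0.7, b of 0.7 or 1.0, g from −0.4 to 0.7. There were 500 runs per scenario.

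**Models compared.** As planned: status ~ biomarker against status ~ biomarker + age, judged by the Wald test at 5%, AIC and BIC. As the aim requires: biomarker ~ age, by linear regression.

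| r (true slope) | b | g | Logistic age coefficient (mean) | p < 0.05 | AIC prefers adjusted | BIC prefers adjusted | Linear slope (mean) | p < 0.05 |
|---|---|---|---|---|---|---|---|---|
| 0.3 | 0.7 | 0 | 0.004 | 6.2% | 17.6% | 0.4% | 0.301 | 100% |
| 0.5 | 1.0 | 0 | −0.003 | 6.6% | 20.2% | 1.0% | 0.501 | 100% |
| 0.7 | 1.0 | 0 | 0.002 | 4.0% | 13.2% | 0.4% | 0.700 | 100% |
| 0 | 0.7 | 0.3 | 0.299 | 99.2% | 100% | 97.8% | 0.001 | 5.8% |
| 0 | 1.0 | 0.7 | 0.702 | 100% | 100% | 100% | 0.001 | 5.6% |
| 0.5 | 1.0 | −0.4 | −0.402 | 100% | 100% | 99.8% | 0.500 | 100% |

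**Reading the table.** The logistic age coefficient estimates g, and the linear slope estimates r. The stated aim concerns r.

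- Rows 1 to 3, missed: age truly shifts the biomarker, but g = 0, so the logistic model has nothing to find.
- Rows 4 and 5, invented: age does not shift the biomarker, yet the adjusted model wins almost always.
- Row 6, reversed: the true slope is +0.50 and the logistic coefficient is −0.40.

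**Analytic check of rows 1 to 3.** When g = 0, the likelihood-ratio statistic for adding one covariate is approximately chi-squared on 1 df.

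- The Wald test rejects in about 5%.
- AIC prefers adjustment when the statistic exceeds 2: P = 15.7%.
- BIC prefers it when the statistic exceeds ln(1,662) = 7.42: P = 0.65%.

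The simulated rates lie around these values, and the analytic values do not depend on r. However strong the age dependence, the planned criterion does not respond to it when g = 0.

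**Second simulation, same sample size.** For r = 0.5 with no direct age effect, age was flagged in 2% of runs (AIC 11%, BIC 1%), which is why the range is given as about 2 to 7%. An ApoE variable with no effect on the biomarker but a direct effect on status was flagged in 100%. Regressing the biomarker again recovered the slope in 100% of runs, with about 5 to 6% false positives.

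**The case against.** The strongest objection is that the sentence names no dependent variable. It could loosely mean separate multivariable models with the biomarker as outcome, and AIC and BIC could be used there too. The article is condensed, refers to a main protocol article in preparation, and elsewhere applies multivariate analysis to spectral data, so its usage is not uniform. That keeps the logistic reading from being certain. It remains the stronger one, because the same paragraph introduces the term for biomarkers in combination as predictors and offers no other model. Nor is this detail left to a fuller plan: a method is named, and it does not fit the aim named beside it.

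A second objection is that the fault may lie in the wording. Comparing adjusted with unadjusted prediction models is sound practice, and only the reference to biomarker distribution misdescribes it. This stands, and rewording is therefore offered as an alternative fix.

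A reader might infer more than the documents support:

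- **That the answer will be wrong.** It can be; whether it is depends on the true structure, which is unknown. The simulated percentages follow from the assumed effects.
- **That the result will govern age- or genotype-specific cut-offs or interpretation.** No such use is planned. The Youden cut-offs come from the univariate models, and none of the three main-objective analyses is said to draw on this step.
- **That every marker is affected alike.** p-tau217, dichotomised, is the outcome of these models, so the point applies chiefly to NfL, GFAP, IL-6 and GDF-15.

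**Conclusion.** The stated method does not answer the stated question. As the paragraph defines its models, covariate coefficients and AIC or BIC gains describe association with p-tau217 status given the biomarker. They are not estimates of how age, sex or ApoE genotype shifts a biomarker.

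At n = 1,662 and under assumed effects, the planned check ranges from almost never detecting a real age effect (BIC favours adjustment in about 1% of runs or fewer) to almost always reporting one that does not exist (97.8 to 100% by BIC). A sign reversal is also possible. Linear regression of the biomarker recovers the true slope throughout.

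The conclusion rests on reading the models as the paragraph defines them. If another model was intended, the sentence still needs to say so. The point is worth correcting but limited: it concerns a supporting biomarker analysis, the baseline data are kept, and the primary 12-month mNTB comparison is untouched.

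**What to change.** State the dependent variable. For each baseline biomarker, regress the level (log-transformed if skewed) on age, sex and ApoE genotype, and report the coefficients with confidence intervals as the influence on biomarker distribution. Keep the covariates and the AIC/BIC comparison in the logistic models for the separate question of whether they improve prediction of p-tau217 status. If that is the only question intended, reword the aim to say so and drop the reference to biomarker distribution.

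The cost is one sentence and, for the five markers measured in all participants (p-tau217, NfL, GFAP, IL-6, GDF-15), five regressions on baseline data already planned. No extra samples or visits are needed.
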